This study is a multi-centered, assessor-masked, three-armed RCT. A convenient sampling method will be adopted for the selection of participants. They will undergo the ophthalmologic visual acuity test for screening. Eligible participants will be randomly assigned to either MY, PE, or wait-list control group through computer software (Randomizer) based on gender, age, and severity of vision loss, in which each group contains the same proportion of the factors mentioned above.

The intervention will be for eight weeks (one hour/day, five days a week), and a follow-up assessment will be carried out six months after the completion of the intervention. The study contains three times evaluations in which the baseline assessment (T0) will be before group division. Post-intervention assessment (T1) will be at the end of the intervention for eight weeks. Follow-up assessment (T2) will be six months after the completion of the intervention. The principal researcher will make unannounced weekly visits to the intervener's class to assess the adherence, consistency, and quality of the intervention. In each classroom, MY or PE, two teaching assistants will support the main instructor in conducting the classes to minimize the risk of injury, such as ankle and knee injuries for the participants.

Randomization method

Stratified randomization will be employed to randomly assign participants based on three factors: age, gender, and the severity of visual impairment. This approach aims to reduce potential confounding effects and enhance the validity of the results.

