However, PE primarily focuses on physical movement and aims at performance, fitness, and skill development. The teaching technique of PE typically is conducted with dynamism and incorporates repetitive movements, drills, and activities without any mindful awareness of breath regulation or meditation. Exercises in the PE group are usually fast-paced and dynamic, with the main goal of developing physical strength, stamina, and agility through organized physical exercises, though the intensity in this study is under control for safety and research purposes [47].

Group 3: Wait-List Control Group

Participants in the wait-list control group will continue their daily routine without receiving either MY or PE training. Three measurements will be taken at T0, T1, and T2 to compare with the other two groups. After the study period, the same MY or PE protocol will be given according to the participants' interests. The participants originally assigned to the PE group will receive MY sessions, whereas those in the yoga group will switch to the PE group. Participants in the wait-list control group can choose either class based on their personal preference after the completion of the intervention.

Blinding

This study is a single-blind RCT. In this study, outcome assessors, who are responsible for outcome measurement, will be blinded to group allocation of the participants. However, it would be hard to blind the participants given the nature of the intervention. Typically, in other research, participants would be informed of their group allocation using an opaque envelope to ensure blinding. However, given that the participants in this study are visually impaired, the opacity of the envelope is irrelevant. The single-blind design may potentially expose the study to risk of bias regarding the outcome expectations of the participants, attrition rate, response rate, and willingness to accept randomization.

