Though blinding the participants will prove challenging, various strategies will be adopted to minimize the risk of participation bias stemming from expectations in case participants know their group allocation, thereby exaggerating the treatment effect. The participants will receive a reminder to refrain from revealing their group assignment to the outcome assessor at any stage of the data collection process. The research hypothesis and details of the study design will not be revealed to the participants. The informed consent form will not claim any certainty about the treatment's superiority [53]. Similar anticipated effects will be declared for both MY and PE groups, such as promoting overall well-being. Participants in both groups will receive the same number of sessions of intervention. Nondisclosure of participants' group allocation will be emphasized to the study assessor at any point in time [54]. Participants in the wait-list control group will be assured to receive either MY or PE training sessions following the same module at the end of the study according to their interests. This method has been widely used and recommended by the Evidence-Based Behavioral Medicine Committee [55].

Adherence

The research assistant will explain the study procedure clearly to make the participants understand the importance of complete attendance before the sessions start. Participants will be instructed to maintain their daily routine and not to initiate any new instructor-led exercise during the whole duration of the study. Every participant will be attentively followed up. Their assessment, as well as its health implications, will be described privately at the end of the research study by health professionals. Participants will receive certificates at the end of the research according to their performance and attendance rate.

Apart from that, all the classes will take place in the blind institutions where the visually impaired students study. Instructors will update the class attendance every day. If any absenteeism, reasons will be recorded and checked by the research coordinator. The research coordinator will intermittently observe the class without prior notification to ensure the quality of the intervention and a positive experience for the participants. After the class, feedback will be taken from participants in case of any suggestions to enhance the intervention quality.

Adverse events

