Prior to commencing any data collection, the data assessors will undergo training regarding the principle of data collection. The data collection procedure will be closely monitored to ensure data quality. In case of any confusion, the data assessors are directed to consult the principal investigator to clear the doubt. If any misinterpretation or misleading of the participants during the subjective psychological questionnaire interview, the data will not be considered.

Data collection at every time (T0, T1, and T2) will need approximately two weeks. Blood collection will be conducted first, followed by ECG recording, questionnaire interview, and physical test. Participants will not be occupied for more than 30 minutes daily for data collection so that their daily study routine will not be interrupted. Laboratory technicians will collect blood in the early morning from 6-9 am with fasting blood. Food and beverage will be provided once the blood collection completes for everyone as breakfast. Each day blood collection will cover around 15-20 participants so that participants do not have to wait too long with an empty stomach. The procedure will be done at the participant’s convenience to complete the follow-up. Data collection for the subjective questionnaire will be in the form of a one-to-one oral assessment, i.e., one participant and one data collector, to protect the participant's privacy.

Data collectors will confirm the time availability of the participants before the visit. The research team will get permission from the authorities before the visit for each data collection. Participants who discontinued the study intervention will be excluded. The principal researcher will keep a record of the reasons for dropping out. Once data is collected, the study investigator will enter the data with the participants’ names coded. The raw data will be stored in a locker, and only the principal investigator can access it. The research assistant will double-check the data entry in case of any mistakes.

Attrition and missing data 

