Given the attrition and missing data in the experiment, the research team will account for a 20% attrition rate and closely monitor the progress of the trial with the aim in mind. To minimize attrition and missing data, it will be emphasized to both research team members and participants that full and complete participation in the intervention is crucial, regardless of the treatment assignment. Follow-ups will be scheduled at participants' convenience, with the assistance of two NGOs, and participants will receive WhatsApp reminders one day before each event.

To handle missing data, we will implement diligent monitoring and provide thorough explanations of study procedures to ensure a positive research experience. Highlighting the altruistic reasons for participation, we will elucidate the significance of maintaining involvement for all the participants. At the end of each follow-up, assessors will explain performance assessments and relevant health concerns to participants [86]. To achieve it, the research team will keenly supervise the whole procedure. The research team will contact participants through the authorities of the two NGOs for follow-up arrangements and conduct follow-up data collection at the participants' convenience.

Additionally, we will identify potential confounding factors and implement controls to mitigate their impact on the study results. This may include adjusting for baseline characteristics, using stratified randomization, and employing statistical techniques such as multivariable regression analysis to control for these factors in the data analysis.

Ethical consideration

This study trial has obtained approval from the institutional ethics committee (IEC) with the Institutional Ethics Committee Clearance Certificate Reference Number: RES/IEC-SVYASA/203/2021. It has been registered in the Clinical Trial Registration of India (CTRI) with the registration number of WHO The Clinical Trials Registry - India: CTRI/2021/08/035853.

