The study procedure will be explained orally to the participants, and thumbprints will be obtained from all the eligible participants before any assessment or intervention. Apart from that, for participants aged from 15 to 18 years old, the research team will obtain oral assent with thumb print, and a consent form will be signed by their legal guardian for their willingness to allow their children to join this research program before the start of any assessment. Participation in this project will be voluntary, and participants can withdraw from the study anytime. The data will be confidential to protect the privacy of the participants. All data will be kept locked and secured, and access will be restricted to only the related research staff. Independent research assistants, without knowing group allocation, will administer the questionnaires orally to each participant and note down the answers in the hard copy. In case of doubt, the chief investigator will clarify the concerned point. Paramedical staff will withdraw blood in a standard hygienic environment. The study and ethical clearance are conducted according to the Declaration of Helsinki guidelines.

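### The query route, the discard rule and assessor feedback weaken the trial's only masking and allow selective loss of interview data

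*Protocol article*

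**What the plan says.** The trial is single-blind. The Blinding section states that "outcome assessors, who are responsible for outcome measurement, will be blinded to group allocation of the participants" and accepts that participants cannot be masked. Two safeguards are given. In Blinding, "The participants will receive a reminder to refrain from revealing their group assignment to the outcome assessor", and nondisclosure is also stressed to the assessors. In Ethical consideration, "Independent research assistants, without knowing group allocation, will administer the questionnaires orally to each participant".

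Three other procedures bear on the same interviews:

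- **Queries.** Under Data collection, when something is unclear, "the data assessors are directed to consult the principal investigator to clear the doubt". Ethical consideration sends questionnaire doubts to the chief investigator. Under Interventions, the principal investigator runs the one-week training of the yoga (MY) and exercise (PE) instructors. Under Design, "The principal researcher will make unannounced weekly visits" to the classes.
- **Discards.** Data collection also says: "If any misinterpretation or misleading of the participants during the subjective psychological questionnaire interview, the data will not be considered".
- **Feedback.** Attrition and missing data says: "At the end of each follow-up, assessors will explain performance assessments and relevant health concerns to participants". Adherence says that each participant's assessment and its health implications "will be described privately at the end of the research study by health professionals".

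**The concern.** HADS and the Oxford Happiness Questionnaire (OHQ) are among the primary outcomes. They are self-reports collected by oral interview from participants who know their group. Masking of the interviewer is the one protection left.

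A query contact who knows the arms, an open-ended rule for dropping interviews, and a required conversation between masked assessors and unmasked participants each give knowledge of arm a route into the data. Interviews dropped more readily in one arm, or for one kind of answer, would bias the comparison between arms. Conversations after T1 could tell an assessor who is in which group, or colour what participants say at T2.

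**Working it through.** The point is procedural and the protocol attaches no figure to it. The main check therefore sets the sections side by side; a short calculation then bounds the size.

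**1. Does the query contact know allocation?** The principal investigator trains the instructors of both active arms (Interventions) and is the person to whom participants report unexpected symptoms (Adverse events). The principal researcher visits classes of about 15 every week (Design, Interventions). If principal investigator, principal researcher and chief investigator are one role, that person sees who attends which class. The safeguards in Blinding and Ethical consideration bind participants and assessors. None covers the person who answers the assessors' questions. Knowledge of allocation is thus a natural inference, not a stated fact.

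**2. What does the discard rule fix?** It is triggered by any misinterpretation or misleading in a psychological questionnaire interview, which plausibly covers HADS and OHQ. The consequence is that the data are left out. The text does not say whether that means the item, the scale or the whole interview, or who decides, and does not require the decision to be masked. At T1 and T2 this is an exclusion after randomisation. It also pulls against Attrition and missing data, whose aim is to keep missing data low.

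**3. Do the two feedback statements agree?** They differ on who gives it (assessors or health professionals) and when (each follow-up or the end of the study).

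**4. Which visits are exposed?** Design puts T0 before group division, so on that order allocation cannot influence the baseline interview (Table 1 lists allocation before T0). Feedback after a visit cannot alter the visit just completed. The exposure is therefore queries and discards at T1 and T2, and feedback between T1 and T2.

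**5. Size if loss is random.** Inputs from Sample size: 36 per arm analysed, 44 per arm recruited, 20% attrition, effect size 0.4 (f or d not stated). After attrition, 44 × 0.8 = 35.2 per arm, already just under 36, so the allowance has no slack for discards. Retained n = 35.2 × (1 − discard rate). The discard rates are assumptions. Power is from the noncentral F (three arms) or the noncentral t (two arms, two-sided), at 5%.

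| Assumed discard rate | n per arm | Power, 0.4 as f | Power, 0.4 as pairwise d |
|---|---|---|---|
| 0% | 35.2 | 96% | 38% |
| 5% | 33.4 | 95% | 36% |
| 10% | 31.7 | 94% | 35% |
| 20% | 28.2 | 91% | 31% |

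One interview is 1/36 = 2.8% of an arm's planned data, or 1/44 = 2.3% of those randomised to it.

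**6. Size if loss is selective.** Suppose k of 36 interviews in one arm are dropped and they lie on average 1.5 SD above that arm's mean (assumed). The mean falls by 1.5k/(36 − k) SD:

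- k = 2: 3/34 = 0.09 SD
- k = 4: 6/32 = 0.19 SD

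On HADS, where higher scores mean more symptoms, that arm would look better. If 0.4 is a pairwise d, these shifts are 0.088/0.4 = 22% and 0.1875/0.4 = 47% of the planned effect.

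**The case against.** The case on the other side is substantial.

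- **Stated safeguards.** Assessors are masked, interviewers are independent, and nondisclosure is stressed on both sides. A reader might infer that masking fails. Nothing says so, and no section has the principal investigator pass allocation to an assessor. This stands.
- **No scoring role.** HADS and OHQ items have fixed response scales and the assistants write the answers down. A reader might infer scoring with knowledge of arm, but the investigator is only asked to clear up a doubt. This stands.
- **No arm-aware deletion.** A reader might infer that interviews are removed by someone who knows the arm. The text does not say who decides, or when. This stands against that reading. It does not rescue the rule, which as written removes data without requiring a masked decision.
- **Feedback may be harmless.** Design uses the label follow-up for T2 and post-intervention for T1, so the feedback might come after the last measurement. It concerns performance and health concerns, not explicitly HADS or OHQ scores, and the same assessor need not see a participant twice. The two feedback statements could also describe two separate events. These points make the T2 risk conditional. The word 'each' still suggests more than one occasion, and the two statements still need reconciling.
- **A condensed article.** Operational detail may sit in a fuller document. That would excuse a missing criterion, but the query route, the discard rule and the feedback are stated procedures.
- **Little loss of power.** Correct for random loss, as the table shows. A reader might infer that completeness fails; random discards at the rates tried do not support this.

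**Conclusion.** The point holds as a weakness, not as a demonstrated failure. The query route, the discard rule and the assessor feedback, followed as written, weaken the only masking the trial claims and allow selective loss of interview data, plausibly including HADS and OHQ.

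The size cannot be derived from the protocol. Random discards of up to 20% cost 5 to 7 percentage points of power. Selective discards of 2 to 4 interviews in one arm could shift its mean by about 0.1 to 0.2 SD under the assumed 1.5 SD offset.

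The conclusion rests on three assumptions: that the person who answers assessor queries knows allocation; that the discard rule covers the primary questionnaires; and, for feedback only, that T1 counts as a follow-up. The discard rule is the firmest part, because it depends on neither the first nor the third.

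**What to change.** 1. **Queries.** At T1 and T2, send assessor questions to an existing team member who has no contact with the classes.
2. **Discard rule.** Replace it. Re-ask the item at the same visit, keep and flag the record, and include it in the primary analysis. Decide any exclusion on coded records without arm, and use it only in a sensitivity analysis.
3. **Feedback.** Reconcile Adherence with Attrition and missing data so that masked assessors give no individual feedback until T2 is complete. A non-assessor gives any feedback needed earlier.

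The article reports data collection as ongoing, so remaining visits can still be protected. For visits already done, retain any discarded interviews and review them without arm.

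The cost is a minor reassignment of tasks within the existing team and a few sentences of text. The drawback is that some imperfect interviews stay in the primary analysis, which the flag and the sensitivity analysis make visible.

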Participants will first be categorized by gender into two groups: male and female. Within each gender group, participants will be further subdivided into two age categories: adolescents (15-17 years) and young adults (18-25 years). Each of these subcategories will then be divided according to the severity of visual impairment: 1) Mild visual impairment: visual acuity worse than 6/12 but better than or equal to 6/18); 2) moderate visual impairment: visual acuity worse than 6/18 but better than or equal to 6/60); 3) severe visual impairment: visual acuity worse than 6/60 but better than or equal to 3/60); 4) Blindness visual impairment: visual acuity worse than 3/60 or a corresponding visual field loss to less than 10 degrees in the better eye with the best possible correction) [47]. Participants in each subgroup at this third level will have their names entered into a computer software program called Randomizer for shuffling. After shuffling, participants will be randomly allocated to one of three groups: the mindfulness-based yoga group, the physical exercise group, or the wait-list control group. The allocation ratio will be 1:1:1. 

Participants recruitment

People with moderate-to-severe VI will be recruited through two primary sources, namely two non-profit rehabilitation organizations (NGOs): the Samarthanam Trust for the Disabled and the Devnar Foundation for the Blind. The sample population will be drawn from the two above-mentioned NGOs by adopting the random sampling method. The intervention will be conducted across multiple sites nationwide, as participants with VI are taken care of by various branches of these two NGOs.

Potential participants will be approached through coordinated efforts with the institutions for the blind. Information sessions will be organized and conducted with the authorization of the governing body and instructors to explain the study's objectives, procedures, and potential benefits. Detailed written materials will be provided, and verbal explanations will be given to ensure comprehension. Participants will have the opportunity to ask questions and discuss any concerns. Informed consent will be obtained from each participant before inclusion in the study, ensuring they fully understand their involvement and the study's requirements. The research will not involve professors or instructors of the visually impaired participants to avoid any perception of obligation among students to participate.

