## Results

Data will be collected and extracted using the standard procedure. The appropriate statistical test will be conducted to analyze the above-mentioned variables using SPSS V. 22.0 software (IBM Inc., Armonk, New York). To find out the differences between groups, an ANOVA test will be adopted; to check within-group changes, a repeated measures ANOVA will be used. The findings will be released subsequent to the study of the data.

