The strengths of this research are: 1) subjective psychological questionnaires correlating with objective, evidence-based assessment will strengthen the study design; 2) multiple centers with a large sample size in different geographical areas will support generating the findings of this research; and 3) a three-group study design will enhance the strength of the study. The active control group (PE group) will be compared with the experimental group (MY group) to discover the potential mechanisms of yoga, especially the effects of mindful awareness on psychological well-being. The wait-list control group will be compared with the other two to reveal the significance of either type of physical activity contributing to general well-being.

Limitations

Potential limitations and their related strategies need to be acknowledged. Subject dishonesty might happen during the interview process to protect one's privacy and social identification, as they might appear to have prosocial behaviors toward interviewers. To ameliorate the effects of bias, the interviewers will inform the participants that private information will be kept confidential, and the interview will be in the form of a one-on-one session. It is crucial to keep in mind that despite the study's design using numerous centers and a sizable sample size from various geographic regions, regional-specific factors like cultural differences, resource accessibility, and customs may still have an impact on the findings. However, in this study, stratified randomization will be adopted to minimize the potential effects of confounding factors such as location, population, educational and cultural differences where the research will take place. Since each center shares certain similarities in terms of setting, such as food habits, living standards, teaching methods, and cultural background, it is reasonable to expect that various confounding factors will have the minimum effects on the results. Additionally, this study will investigate the evaluation and implementation of the MY or PE protocol. However, social support will not be considered as one factor for randomization. Therefore, it will be possible if there will be varying levels of social support among the three groups. Dropouts and missing data may also pose a risk to internal validity. The strategy to reduce the dropout rate has been discussed previously in the section named "attrition and missing data".

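### Excluding everyone who stops the intervention turns the randomised comparison into one of completers, and the rule can act only in the two active arms

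*Protocol article*

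**What the plan says.** All references are to the protocol article.

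- **Data collection** gives the rule without qualification: "Participants who discontinued the study intervention will be excluded". It adds that reasons for dropping out are recorded. It does not say what people are excluded from, or how much missed attendance counts as discontinuing.
- **Ethical consideration** treats leaving the study as something separate: "Participation in this project will be voluntary, and participants can withdraw from the study anytime".
- **Group 3: Wait-List Control Group**: "Participants in the wait-list control group will continue their daily routine without receiving either MY or PE training". This arm is only measured, at T0, T1 and T2.
- **Attrition and missing data** begins its account of handling with "To handle missing data, we will implement diligent monitoring and provide thorough explanations of study procedures to ensure a positive research experience" and continues with explanations, reminders and scheduling. It ends with possible adjustment for baseline characteristics and multivariable regression, offered against confounding.
- **Results** gives the between-group analysis: "To find out the differences between groups, an ANOVA test will be adopted". Repeated measures ANOVA is used within groups. No analysis population is named.
- **Limitations** concedes that "Dropouts and missing data may also pose a risk to internal validity", and refers back to the attrition section.

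**The concern.** Randomisation makes the three arms comparable at allocation. A rule that then removes people according to whether they kept attending gives up that protection.

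The active arms ask for 40 one-hour classes over eight weeks. If those who stop tend to be those who are struggling or not improving, removing them makes both active arms look better against wait-list, where nobody can be removed for this reason.

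The second hypothesis, that MY is superior to PE, is exposed too. The article describes MY as slow and non-competitive and PE as dynamic and aimed at performance, so the numbers who stop and their reasons may differ. The direction of that bias cannot be known in advance. Because discontinuation has no threshold, each exclusion is also a matter of judgement in a trial where participants and instructors know the allocation.

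This is not a detail left to an analysis plan: the article itself fixes the exclusion.

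**Working it through.** **1. Does anything override the rule?** Data collection excludes those who stop. The attrition section offers prevention, plus covariate adjustment that may be used; adjustment cannot bring back people whose outcomes are absent. Results names ANOVA and repeated measures ANOVA, which in their usual form omit anyone without the outcome. Limitations points back to prevention. No section commits to following or analysing those who stop.

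**2. Is the rule one-sided?** "The allocation ratio will be 1:1:1", so 44 per arm. Discontinuing an intervention is possible in MY and PE, and not possible in wait-list, which receives none during the study. Wait-list members can still withdraw or be lost, but that route is open to all arms.

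**3. Numbers.** The only related figure in the article is 20% attrition in Sample size: 36 × 1.2 = 43.2, rounded up to 44 (36/0.8 would give 45). How 36 follows from the effect size is a separate matter and is not used here. If the whole 20% were discontinuation, each active arm would keep 44 × 0.8 = 35.2, about 35, against 44 in wait-list. That is 35 + 35 + 44 = 114 of 132.

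**4. Size of the bias.** Assumptions, none taken from the article:
- there is no true effect and outcomes are standard normal;
- a fraction q of one active arm is excluded, namely those highest on a latent tendency to stop;
- that tendency correlates r with a worse outcome;
- nobody is excluded from wait-list.

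With c = Φ⁻¹(1 − q), the mean of those retained shifts in the favourable direction by r × φ(c)/(1 − q). For q = 0.20, φ(c)/(1 − q) = 0.280/0.80 = 0.35, so r = 0.3 gives 0.105 SD and r = 0.5 gives 0.175 SD. Type I error comes from 20,000 simulated two-sided 5% t tests against 44 wait-list participants.

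| Excluded | r = 0.2 | r = 0.3 | r = 0.5 |
|---|---|---|---|
| 10% | 0.039 SD; 5.3% | 0.058 SD; 5.7% | 0.097 SD; 7.0% |
| 20% | 0.070 SD; 6.4% | 0.105 SD; 7.4% | 0.175 SD; 12.2% |
| 30% | 0.099 SD; 7.0% | 0.149 SD; 10.0% | 0.248 SD; 18.6% |

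**5. Against the planned effect of 0.4.** The article does not say what kind of effect size this is.
- As a standardised mean difference, the 20% row at r = 0.3 to 0.5 is 0.105/0.4 = 26% to 0.175/0.4 = 44% of it.
- As Cohen's f over three groups, the largest pairwise difference lies between 0.4 × 6/√8 = 0.85 SD and 0.4 × √6 = 0.98 SD. The share is then 0.105/0.98 = 11% to 0.175/0.85 = 21%.

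**6. MY versus PE.** With equal exclusion and equal r the shifts cancel. If one arm loses 30% and the other 10%, the arm that loses more gains 0.149 − 0.058 = 0.09 SD at r = 0.3, or 0.248 − 0.097 = 0.15 SD at r = 0.5.

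**The case against.** The strongest reply is that the word excluded has no object. The sentence sits under Data collection and may mean only that those who stop are not assessed further. Their T0 data, and for some T1, would still exist, and an analysis plan could specify an as-randomised analysis with a method for missing data. Table 1 also schedules adherence at T1 and T2, which fits poorly with removing every non-adherer. The ambiguity is real. But on either reading the people who stop are missing from the comparison the article describes, and not assessing them creates missing data that cannot be recovered later.

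The size is also open to challenge, and much of that stands. The 20% is overall attrition with no cause given, not a rate of stopping classes. The correlation has no source in the article. People may stop because of timetables, transfer or injury unrelated to outcome, in which case the bias shrinks or could change direction. The share of the planned effect roughly halves if 0.4 is Cohen's f. These points limit the number, not the defect.

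It is also fair that the attrition section mentions regression adjustment, and that the Discussion promises to evaluate attrition as a source of bias. Adjustment could reduce selection on measured baseline factors. Neither step returns the excluded people to the analysis.

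**Conclusion.** The concern holds, and the sentence must be changed. As written, the plan compares those who completed MY or PE with an unselected wait-list group. That conclusion follows from the text and needs no assumption.

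The size does need assumptions. A spurious benefit against wait-list of 0.04 to 0.10 SD with 10% excluded, or 0.07 to 0.18 SD with 20%, is a reasonable illustration if stopping correlates 0.2 to 0.5 with a worse outcome. For MY versus PE neither size nor direction can be predicted.

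**What to change.** Replace the sentence in Data collection with one to this effect: *Participants who stop attending the intervention remain in follow-up unless they withdraw from the study, are assessed at T1 and T2, and are analysed in the arm to which they were randomised.* Then:

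- Make the as-randomised analysis primary. A likelihood-based mixed model on all available data is one suitable method; a baseline-adjusted comparison by assigned arm would also answer the point.
- Keep completers as a labelled sensitivity analysis, with discontinuation defined in advance.
- Report the numbers who stopped and their reasons by arm; the reasons are already to be recorded.
- For the 62 participants already recruited, keep all data collected on anyone who stopped, and obtain T2 where this is still possible and they agree. For those who started in August 2022, eight weeks plus six months puts T2 at about April 2023, and the article does not show whether that window is still open.

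The core change is one sentence. The rest means amending the analysis text, adding a sensitivity analysis and assessing some people who would otherwise have been dropped. Assessments are arranged through the participants' institutions and T1 and T2 rounds are already scheduled, so few if any new visits should be needed, although the Abstract reports difficulty with logistics and authorisations. The estimated effect may be less favourable, because it will include people who did not finish the programme.
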